### Data collection

Participants will go through four assessment periods at baseline, 6 weeks (post-program), 6 months, and 12 months follow-up. The training and clarification session will be completed by telephone to ensure participants are equipped with the skills to access the intervention contents. Before the first, third and fourth assessment periods, eligibility will be checked against inclusion and exclusion criteria through a telephone screening/re-screening call, 1 week prior to each visit. Participant's timeline is shown in Figure 3.

*Assessment* 1 (baseline): Clarification session about the study. If participants are still interested in enrolling in the study, eligibility will be checked, and they will be asked to fill out an informed consent form. Randomization and allocation to one of the four arms of the trial will be performed. Data on demographics and potential psychological moderators will be collected. A battery of psychological and behavioral questionnaires will be completed online using google forms (in one-week time) – running behavior (i.e. frequency and minutes per week), motivations, basic psychological needs, motives and gains, self-regulation skills, passion, flow, and vitality. This task is estimated to take approximately 1 h, but participants will be able to do breaks and return later to complete the psychometric evaluation during that week. Debrief on how to use the KOR web-based intervention content – the toolkit (approximately 1 h).

*Assessment*s 2 and 3 (intervention's end and 6-month follow-up). Email reminder prior to this evaluation period will be sent. The same battery of psychological and behavioral questionnaires will be completed online using google forms (in one-week time) – running behavior (i.e. frequency and minutes per week), motivations, basic psychological needs, motives and gains, self-regulation skills, passion, flow, and vitality –, and will take approximately 1 h.

*Assessment* 4 (12-month follow-up). Running behavior maintenance will be assessed through a telephone call, asking participants whether they keep running at their initial level or higher, or not.

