### Analytical strategy

Statistical analysis will be performed using SPSS Statistics version 25.0 (SPSS Inc., an IBM Company, Chicago IL, USA). Descriptive statistics will be calculated (mean, standard deviation and range). Repeated measures with Bonferroni corrections for adjusted comparisons will be used to examine differences between each intervention group(PNMC or SRM) and controls (i.e. free recreational runners), at all assessment points, in the primary and secondary outcomes measured. Statistical significance will be set at *p* < 0.05.

Mediation analysis, will test the psychological mechanisms underlying changes in running behavior from baseline to post program, 6 and 12 months. Multilevel modeling will be used to determine the SRM intervention effect on these motivational variables, with intervention group (SRM vs. Control group) as the between-subject factor and change in self-regulation and competence for running at baseline, 6–8 weeks, 6months and 12 months, serving as dependent variables. If necessary, multiple imputation methods will be implemented to provide robust results for primary and main secondary outcomes.

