### Power calculations and sample size estimation

Two types of sample size calculations were made: (a) using the primary outcome – running minutes and (b) using secondary outcomes, in particular, changes on key psychosocial variables. Regarding our primary outcome, we have used vigorous physical activity for our calculations. A small effect size (Cohen's *d *= 0.23) is expected, a value previously registered in studies with intrinsic motivation interventions (Ntoumanis et al., 2020; Sheeran et al., 2020). Considering a power of 0.8 with two-tailed analysis, we estimated that each intervention group should have 37 (*p *= 0.05) or 55 participants (*p *= 0.01). Concerning our secondary outcomes, we are expecting effects sizes ranging from 0.23 to 0.73, based on previous reports (Ntoumanis et al., 2020; Sheeran et al., 2020). Thus, assuming an effect size of 0.50, 18 subjects/group will be required to detect significant differences at *p *= 0.05 and 28 for *p *= 0.01. Given that the primary outcome is expected to have a smaller effect size, and expecting a dropout rate of 15% at follow-up, we estimate that approximately 55 subjects/group are needed at baseline (for *p *= 0.05). Thus, recruiting 220 participants will ensure high statistical power for our primary analyses, extending its power to the secondary analyses.

Trial results will be published in peer-reviewed scientific journals and in several international and national scientific conferences. The website will be our central media to promote the dissemination of the results to the general public. Other media will be reached through university partners and website.

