#### Pilot study participants

Pilot participants were recruited among the running community through online advertisement. Study procedures were equivalent to those defined for the RCT, except that participants were not randomized, following the path of the study as if they were included in the intervention group. Participants were informed about the results of this pilot by individual reports.

The pilot feasibility study was a 6-week non-controlled trial without the follow-up. Considering an expected effect size of 0.23, 55 subjects per arm should be required in the main trial to detect significant differences at *p *= 0.05 (see sample size calculations for the main trial). Bearing in mind the rule of thumb for pilot sample size (Bell, Whitehead, & Julious, 2018), for an 80% powered main trial, with an expected medium effect size, the pilot should have between 10 and 15 subjects per arm.

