#### Pilot participant characteristics

The CONSORT diagram for the pilot is shown in Figure 5. In total, 18 participants were enrolled and completed the baseline assessment. Of those, 3 dropped out during the intervention, allegedly due to time constraints and injuries; 15 participants finished the 6 week-intervention, 7 the post-program questionnaire, and 14 the overall study satisfaction questionnaire.

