## Discussion

This paper presents the rationale, development, study design, methods and pilot application of the KOR trial, aimed at testing the effect of the intervention on the maintenance of recreational running behavior over time, after being voluntarily initiated by community-dwelling adults in the previous 3 months. This ‘light-touch’ intervention is unique in that it approaches running behavior and its sustainability, delivered in a digital format, and based on strong theoretical foundations.

We hypothesize that the sustainability of running behaviors will be higher in the SRM groups compared to the control group. Change in running behavior (e.g. frequency and minutes of running per week) and secondary outcomes related to the quality of the running experience (e.g. passion, flow, vitality) will be used as the dependent variables.

Additionally, the results of the pilot feasibility study, intended at testing intervention adherence, participant satisfaction, and questionnaire acceptance, were also presented. Overall, the pilot study indicated that the intervention has good acceptability, feedback was very positive, but toolkit interaction decreased after the first weeks, which is common in web-based interventions (Baumel & Yom-Tov, 2018). Moreover, the generalized use of other running-related devices, applications and communities may have overlapped with the anticipated content of the toolkit, challenging participants’ interaction. The completion ratio of the post-program questionnaire was low, maybe due to its extension and burden, but also because its timeline ended near the summer break.

The main trial should reduce questionnaire length and burden, and include interface with usual monitoring gadgets and apps (APIs), to increase data detail and prevent ‘unnecessary’ data insertion by the participants. Features such as feedback and social sharing, added to the goal setting features already integrated in the toolkit, may also increase attractiveness (Hosseinpour & Terlutter, 2019).

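### The 15% loss allowance ignores the pilot's 61% non-return of the 6-week questionnaire that carries the primary outcome, and the RCT methods still place the running items in a one-hour battery

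*Protocol article*

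**What the plan says.** All references are to the protocol article.

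- **Power calculations and sample size estimation.** For the primary outcome, with d = 0.23, the article states "we estimated that each intervention group should have 37" participants at the 5% level. It then allows for loss, "expecting a dropout rate of 15% at follow-up", and arrives at about 55 per group at baseline, 220 in total. No source is given for 15%.
- **Assessments; Data collection.** The primary outcome is self-reported running frequency and minutes per week at baseline, end of intervention and 6 months. At the two later points these items sit in the same online battery as the psychological scales, to be completed within a week, "and will take approximately 1 h". Only the 12-month question, whether the participant still runs at least at the initial level, is asked by telephone.
- **Pilot study participants.** Apart from the absence of randomisation, pilot procedures are described as equivalent to those of the RCT.
- **Pilot participant characteristics.** Of 18 enrolled, 3 dropped out during the intervention; "15 participants finished the 6 week-intervention, 7 the post-program questionnaire, and 14 the overall study satisfaction questionnaire".
- **Pilot program evaluation.** 83.3% found the questionnaire too long.
- **Discussion.** The low completion is put down, tentatively, to length and burden and to timing near the summer break. The recommendation follows: "The main trial should reduce questionnaire length and burden". The Abstract says the same.

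**The concern.** A dropout inflation exists so that enough participants provide the primary outcome. What matters is therefore the proportion who return the instrument holding that outcome, not the proportion who formally leave. Testing the questionnaires was one of the pilot's stated purposes, and it returned a poor result for exactly this instrument at exactly the 6-week time point. The RCT sections nevertheless keep the one-hour battery with the running items inside it, and keep 15%.

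If return in the RCT came anywhere near the pilot's, more than half of the 6-week primary-outcome data would be absent. The multiple imputation mentioned under Analytical strategy does not recreate that information, and its results would lean heavily on assumptions about those who did not respond.

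**Working it through.** **Inputs.** Two-sided 5% level ("Statistical significance will be set at *p* < 0.05"; "Considering a power of 0.8 with two-tailed analysis"); d = 0.23; 37 evaluable and 55 at baseline per group; 15% loss; pilot counts 18 enrolled, 3 dropped out, 7 post-program questionnaires, 14 satisfaction questionnaires.

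**1. The article's own inflation.** 37 / (1 − 0.15) = 43.5, so 44 per group, not 55. Taken at face value, the step from 37 to 55 tolerates a loss of 1 − 37/55 = 32.7%. With 15% loss, 55 leaves 55 × 0.85 = 46.75, about 47.

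**2. Pilot rates (exact binomial 95% CIs).**
- Labelled dropout: 3/18 = 16.7% (3.6–41.4%). If the true rate were 15%, P(3 or more of 18) = 0.52, so this is compatible with the plan, although reached within 6 weeks.
- Primary-outcome questionnaire not returned: 11/18 = 61.1% (35.7–82.7%); equivalently, return 7/18 = 38.9% (17.3–64.3%). If true loss were 15%, P(11 or more of 18) ≈ 0.00001. If it were 32.7%, the probability is about 0.012.
- Satisfaction questionnaire returned: 14/18 = 77.8% (52–94%), i.e. 22% loss.

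The non-return interval excludes 15% and, narrowly, the 32.7% that 55 per group can absorb.

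**3. Consequence for evaluable numbers.** Evaluable per group = 55 × return; power is for a two-sample t test, two-sided 5%, d = 0.23.

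| Loss | Evaluable per group | Against 37 | Power at d = 0.23 |
|---|---|---|---|
| 0% | 55 | above | 22% |
| 15% | 55 × 0.85 ≈ 47 | above | 20% |
| 22% (4/18) | 55 × 14/18 ≈ 43 | above | 18% |
| 61% (11/18) | 55 × 7/18 ≈ 21 | below | 11% |

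**4. Separating this from the error in the base figure.** For two groups, n = 2 × ((1.960 + 0.842)/0.23)² ≈ 297 per group, so 37 does not follow from d = 0.23. That is why power is 22% even with no loss. To isolate the effect of missing data, take instead the effect that 37 per group would detect with 80% power, d ≈ 0.66. At that effect, 47 per group gives 89%, 43 gives 86% and 21 gives 55%.

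**5. Illustration only.** Keeping 37 evaluable at the pilot return rate would need 37 / (7/18) = 95.1, so 96 per group. This is not a corrected sample size, because 37 is itself unsupported.

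**The case against.** Several points on the other side are sound.

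- **Dropout itself is not contradicted.** The article plans for dropout, and pilot dropout was 17%. A reader might infer that the pilot refutes the 15% as a dropout rate; it does not. What remains is that dropout is the wrong quantity to inflate for when the outcome sits in a questionnaire that most pilot participants did not return.
- **The authors intend to change the battery.** The Abstract and Discussion call for a shorter questionnaire and for data from running devices and apps, and the Conclusion promises adjustments. It would be too strong to say that the trial has chosen to keep the pilot battery. The supportable statement is that Data collection and the sample size section do not reflect the intention.
- **55 has slack.** It survives 15% and 22% loss with more than 37 left. Only losses beyond about 33% break it, and the lower limit for pilot non-return, 35.7%, lies just past that.
- **The low power at d = 0.23 is mostly another defect.** Going from 22% at full data to 11% at the pilot return rate is a real loss, but most of the gap from 80% was there already.
- **The cause is not established.** That 14 of 18 answered the satisfaction questionnaire suggests that length mattered, without proving it. The summer break is offered as well, and the pilot also included interviews. Nothing shows that non-responders had stopped running.
- **The pilot is weak evidence on the rate.** It had 18 people, all on the intervention, with average running experience of 6.3 years and no follow-up beyond 6 weeks. It says nothing about return in controls or in runners from the organised programme.

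These points limit how far 61% can be projected. They do not supply a basis for 15%.

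**Conclusion.** The concern holds in a limited form. The 15% allowance has no stated source, and the only evidence in the article on return of the primary-outcome instrument is 7 of 18 at 6 weeks, whose interval excludes it. The sections that fix the RCT's data collection and sample size were not brought into line with that result or with the article's own recommendation to shorten the questionnaire.

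The size depends on the loss assumed: about 47, 43 or 21 evaluable per group at 15%, 22% or 61%. Only the last falls below the article's 37. The 61% is a stress value, and the article does not support a prediction that most of the RCT's primary-outcome data will be missing. The calculation assumes equal return across groups and a simple two-group comparison at one time point. The 12-month telephone question is outside the argument.

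**What to change.** **Data collection.** Collect running frequency and minutes first, on a short form separate from the psychological battery, in all four groups at 6 weeks and 6 months, and follow up those who do not respond. This needs a brief added contact at 6 weeks: only an email reminder is planned there, and the planned calls come one week before the first, third and fourth assessments, so they cannot serve to chase unanswered forms. State the battery length actually intended for the RCT.

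**Power calculations and sample size estimation.** Replace the single 15% by a range of primary-outcome loss informed by the pilot: for example 15% to 61%, with 22% (from the satisfaction-questionnaire return, 95% CI for return 52–94%) as an illustrative middle value. It is illustrative because return of a short running form was not measured. Report evaluable numbers and power across the range, as in the table above, and say plainly that the base figure of 37 needs its own correction, since retention alone will not restore 80% power at d = 0.23.

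**Cost.** Some form redesign, modest extra contact work, and stated precision that looks less favourable than it does now.

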### Pilot feasibility study

This pilot study is focused on intervention adherence and participant satisfaction, in order to establish the feasibility and acceptability of the web-based intervention toolkit and questionnaires. Besides eligibility, baseline and post-program questionnaires, participants were interviewed about their overall experience with questionnaire filling and toolkit (Smailes et al., 2016). Additionally, toolkit usage analytics were obtained. The pilot feasibility study was conducted in order to better inform the final program and procedures. This study, as well as implications for final protocol are briefly described here.

#### Pilot study participants

Pilot participants were recruited among the running community through online advertisement. Study procedures were equivalent to those defined for the RCT, except that participants were not randomized, following the path of the study as if they were included in the intervention group. Participants were informed about the results of this pilot by individual reports.

The pilot feasibility study was a 6-week non-controlled trial without the follow-up. Considering an expected effect size of 0.23, 55 subjects per arm should be required in the main trial to detect significant differences at *p *= 0.05 (see sample size calculations for the main trial). Bearing in mind the rule of thumb for pilot sample size (Bell, Whitehead, & Julious, 2018), for an 80% powered main trial, with an expected medium effect size, the pilot should have between 10 and 15 subjects per arm.

#### Results of the pilot feasibility study

Due to recruitment problems, the eligibility criteria for participants with more than three months of running experience were more flexible. All other recruitment procedures were equivalent to the RCT.

#### Pilot participant characteristics

The CONSORT diagram for the pilot is shown in Figure 5. In total, 18 participants were enrolled and completed the baseline assessment. Of those, 3 dropped out during the intervention, allegedly due to time constraints and injuries; 15 participants finished the 6 week-intervention, 7 the post-program questionnaire, and 14 the overall study satisfaction questionnaire.

**Figure 5. F0005:**
[figure not shown]
CONSORT diagram.

Participants (*N* = 18, 33% female), between 25 and 54 years-old (average 42.1 yrs.), were generally self-perceived as healthy (94%), highly educated (78%), and lived mostly in the Lisbon area (83%). Participants reported to run an average of 27 km and 4.4 h per week. Running experience ranged from 1 month to 30 years (average 6.3 yrs.). Most participants (88.9%) wore a running monitoring device to keep track of their running, social sharing and coaching, and 94.4% included other types of exercise in their training regime, such as warm-up and stretching, weight training or calisthenics, exercise classes or biking. A total of 61.1% used social media for motivation, education, interaction and coaching purposes.

#### Pilot adherence and program usage

From the 18 participants allocated to the intervention, 17 (94.4%) logged at least once, 50% logged once, and 22.2% twice. Only 6 (33.3%) completed the first session. Participants’ session completion decreased at sessions two (*N *= 5; 27.8%), five (*N *= 4; 22.2%), and only three participants (16.7%) completed sessions from eight to eleven. During the course of the program 12 participants (66.7%) logged at least one race (1–15 races, average 5.2), and the average run lengthened 9.4 Km (4–14 Km).

#### Pilot program evaluation: participant satisfaction

Overall, participants understood the purpose of the study, the concepts underlying the questionnaires and the toolkit, and felt supported by the research team. Most participants (83.3%) found the questionnaire too long. Participants generally found the toolkit website to be attractive and user friendly, classifying their overall experience with the study as positive. Most of the interviewed participants already used a running monitoring app, so they found the program to be less intuitive, repetitive in some questions and missing out important aspects such as ‘time of day, speed/ pace, and altimetry’. Additionally, participants reported problems with platform adjustment that led to ‘information overlap when used on cellphone’, the fact that ‘it didn't keep data inserted in previous sessions’ and ‘errors in google docs that forced them to restart the questionnaire’.

Three participants suffered injuries during the intervention period (25%). Two had muscular running-related injuries in the lower limbs and one had a foot trauma injury while playing football.

This pilot study had limitations that need to be considered, Due to recruitment constraints, the final sample included long time runners, which may differ from beginners, targeted by the RCT protocol. The low sample size and the absence of follow-up hindered further interpretation about the efficacy of the toolkit as it is.

## Ethics and dissemination

The study protocol was approved by the Ethics Committee of the Faculty of Human Kinetics, University of Lisbon (CEFMH 3/2018) and will be conducted in accordance with the declaration of Helsinki for human studies (World Medical Association, 2013). All participants will be informed about the possible risks of the investigation before giving their written informed consent to participate. Data from google forms (questionnaires), the intervention quizzes and toolkit analytics will be handled and stored in excel and SPSS files in a secure faculty server for ten years. Data will then be destroyed. All personal data will be anonymised at source. There will be no names or other identifiers in the manuscripts and qualitative descriptions whatsoever. Data will only be linked back to the individual via a separately stored coding system. Interventions will be discontinued if they are reported detrimental. Protocol deviations, violations and serious adverse events will be recorded by trial staff and monitored by the principal investigator ([name]) (MRC, 2017).

## Discussion

This paper presents the rationale, development, study design, methods and pilot application of the KOR trial, aimed at testing the effect of the intervention on the maintenance of recreational running behavior over time, after being voluntarily initiated by community-dwelling adults in the previous 3 months. This ‘light-touch’ intervention is unique in that it approaches running behavior and its sustainability, delivered in a digital format, and based on strong theoretical foundations.

We hypothesize that the sustainability of running behaviors will be higher in the SRM groups compared to the control group. Change in running behavior (e.g. frequency and minutes of running per week) and secondary outcomes related to the quality of the running experience (e.g. passion, flow, vitality) will be used as the dependent variables.

Additionally, the results of the pilot feasibility study, intended at testing intervention adherence, participant satisfaction, and questionnaire acceptance, were also presented. Overall, the pilot study indicated that the intervention has good acceptability, feedback was very positive, but toolkit interaction decreased after the first weeks, which is common in web-based interventions (Baumel & Yom-Tov, 2018). Moreover, the generalized use of other running-related devices, applications and communities may have overlapped with the anticipated content of the toolkit, challenging participants’ interaction. The completion ratio of the post-program questionnaire was low, maybe due to its extension and burden, but also because its timeline ended near the summer break.

The main trial should reduce questionnaire length and burden, and include interface with usual monitoring gadgets and apps (APIs), to increase data detail and prevent ‘unnecessary’ data insertion by the participants. Features such as feedback and social sharing, added to the goal setting features already integrated in the toolkit, may also increase attractiveness (Hosseinpour & Terlutter, 2019).

